## Abstract

**Introduction::**

Carpal tunnel syndrome (CTS) is the most common entrapment neuropathy that causes hand discomfort and work disability. Since no satisfactory conventional treatments for mild to moderate CTS exist, we apply complementary alternative medicine (CAM) to this problem. Laser acupuncture (LA), a new, non-invasive therapy which uses low-level-laser therapy (LLLT) in acupuncture could help to manage CTS. However, only one small randomized, double-blind and crossover trial had been conducted, which is not enough to provide an evidence-based assessment of the effects of LA on CTS.

**Objectives::**

The aim of this study protocol is to investigate the efficacy of LA therapy on patients with mild to moderate CTS through sonography of the median nerve and offer clear parameters of LLLT.

**Methods::**

This study protocol is a prospective double-blind randomized controlled trial. Forty subjects aged 20 to 80 years old and diagnosed as having mild to moderate CTS will be randomly assigned to the intervention group (real LA, 3-sessions a week for 2 weeks) and control group (sham LA, 3-sessions a week for 2 weeks). All subjects will be asked to wear night splints as the fundamental management approach. The laser parameters will include a wavelength of 808 nm, power output of 300 mW and power density of 300 mW/mm^2^, with ten seconds of treatment for each acupuncture point (PC4, PC6, PC7, PC8, LI4, LI10, LI11, HT3, HT7, and LU10). Sham LA treatment will be applied without any laser power output. The primary outcome will be based the Boston Carpal Tunnel Syndrome Questionnaire and secondary outcomes included a visual analog scale, cross sectional area of median nerve by sonography and electrophysiological test before interventions and after 2, 4, 8, 12 weeks postintervention.

**Trial registration::**

ClinicalTrials.gov (Identifier: NCT03580265).

## Introduction

1

Carpal tunnel syndrome (CTS) is the most common entrapment neuropathy resulting from compression of the median nerve (MN) as it passes through the carpal tunnel at the wrist.^[1]^ The prevalence of CTS is around 4% in Sweden^[2]^ and pain, numbness, or tingling in the thumbs, index, and middle fingers are the most common symptoms. Atrophy of the thenar muscle and weakness of pinch grasp may occur in patients with moderate to severe CTS.^[3]^ Hence, CTS often causes work disability.^[4]^ Although the pathophysiology of CTS is complicated, studies agree that persistent high pressure within the carpal tunnel compresses the MN and induces compression-related ischemia neuropathy.^[5]^

The treatments for CTS can be divided into conservative treatment and surgery. The conservative methods are suggested for mild to moderate CTS, including rest, nonsteroidal anti-inflammatory drugs (NSAIDs), splinting, corticosteroid injections, vitamin B, physical therapy, and so on.^[6,7]^ Although many conservative treatments are available, they fail to achieve satisfactory midterm and long-term effects.^[8]^ In addition, surgery is an invasive procedure with uncertain cost-effectiveness^[9]^; hence, surgery is only suggested for severe CTS or patients with unsatisfactory responses to conservative treatment. As a result, new conservative methods should be proposed to promote the success rates of treating mild to moderate CTS.

Low-level laser therapy (LLLT) is a non-invasive method and can promote wound healing, peripheral nerve regeneration, pain relief, and further reduction of inflammation.^[10]^ LLLT general applies wavelengths ranging from 600 to 1070 nm and power outputs ranging from 1 mW to 1000 mW.^[11]^ Some systematic reviews and meta-analysis studies have reported the significant efficacy of LLLT in different clinical conditions, such as temporomandibular disorders, fractures and plantar fasciitis.^[12–14]^ The therapeutic efficacy of LLLT for CTS was postulated in 1997–1998^[15,16]^ and studies have both investigated LLLT alone and compared it to other conservative treatments. Although most studies showed that LLLT leads to pain relief and hand function of CTS,^[17–22]^ a few studies found no significant benefits for CTS.^[23]^ A recent systematic review and meta-analysis revealed very short-term effects of LLLT for CTS.^[24]^ Lately, many clinicians have used LLLT on acupuncture points, which is called laser acupuncture (LA), to treat many clinical problems, such as musculoskeletal pain, lateral epicondylitis, headaches, etc.^[25]^ In contrast with traditional acupuncture needles, LA is a non-invasive therapy that does not cause tingling/pain during procedures.^[25,26]^

The application of LA for CTS is very rare and the first randomized, double-blind, placebo-control, crossover trial enrolled only 11 patients, as reported in a PubMed study in 2002.^[17]^ The result showed that patients with mild to moderate CTS experienced pain relief, improved Phalen's/Tinel's signs and sensory nerve conduction after LA therapy. However, the above study only investigated a few cases and applied a crossover design. Thus, the above findings do not confirm the definite therapeutic effect of LA for CTS. The purpose of our study aims to evaluate the clinical effect of LA for mild to moderate CTS through sonography of the MN and to offer clear parameters of LLLT.

## Material and method

2

### Ethics approval

2.1

The study protocol was approved by the Institutional Review Board of Tri-Service General Hospital (TSGHIRB: 1-107-05-062) and was registered with ClinicalTrials.gov (Identifier: NCT03580265). All recruited participants will be informed about the study procedure and provide informed consent before the study begins. The methods performed on each participant will follow the approved ethical guidelines. Personal information and study data will be collected and maintained in an independent closet and computer file with a password in order to protect personal data.

### Study design

2.2

This study protocol was designed as a prospective, randomized, double-blind, controlled trial according to the CONSORT 2010 statement (Fig. 1)^[27]^ and will be conducted at Tri-Service General Hospital in Taiwan in 2019. The recruited participants will be randomly assigned to the intervention group (real LA) or control group (sham LA) via computer-generated random numbers (1:1 ratio) using Microsoft Excel. If the patients are diagnosed with bilateral CTS, both wrists will be assigned to the same group. All subjects will wear night splints at least 8 h per night through the whole study period as the fundamental management approach.^[28]^ The LA device (“TRANS” Laser Phototherapy Device, TRANSVERSE INDUSTRIES CO., LTD, Taiwan) is like a pen (Fig. 2). A semiconductor was made of gallium–aluminum–arsenide (Ga–Al–As) with a wavelength of 808 nm, power output of 300 mW and power density of 300 mW/mm^2^ (following the guidelines of Jekins and Carroll).^[24,29]^ Real LA and sham LA will be applied by the same physician who is a licensed Chinese medicine practitioner in Taiwan. The ten acupuncture points include PC4 (Ximen), PC6 (Neiguan), PC7 (Daling), PC8 (Laogong), LI4 (Hegu), LI10 (Shousanli), LI11 (Quchi), HT3 (Shaohai), HT7 (Shenmen), LU10 (Yuji) (Fig. 2 and Fig. 3). Some of these points have used in other CTS studies.^[30,31]^ These acupoints are located according to the WHO Standardized Acupuncture Point Localization guidelines.^[32]^

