#### Sample size

2.4.1

The necessary number of subjects required for our study is based on a previous study of the effects of LLLT for CTS.^[22]^ The sample size was calculated with a power of 80% (1 – β = 0.8), statistical significance (α = 0.05) of 95% and a dropout rate of 20%. As a result, this study will require at least 40 wrists.

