### Statistical analysis

2.6

All statistical analyses will be performed with IBM SPSS Statistics Version 24. All data will be presented as mean ± standard error. The pair *t* test will be used to evaluate and compare before and after treatments within each study group. The independent *t* test and chi-square will be used to evaluate and compare before and after treatments between two groups. All statistical tests will be two-tailed and a *P*-value less than .05 is considered to be a statistically significant difference.

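### Patients are randomised with both wrists in one arm, but the sample size counts wrists and only ordinary tests are named; if wrists are analysed, the nominal 5% test is anti-conservative

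*Protocol article*

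**What the plan says.** Four places in the protocol article bear on the unit.

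- **Section 2.2, Study design.** The person is allocated: "The recruited participants will be randomly assigned to the intervention group (real LA) or control group (sham LA"), in a 1:1 ratio. For bilateral disease, "If the patients are diagnosed with bilateral CTS, both wrists will be assigned to the same group". Each randomised patient can therefore bring one or two wrists.
- **Section 2.4.1, Sample size.** With 80% power, α = 0.05 and 20% dropout, "this study will require at least 40 wrists". No effect size or standard deviation is given, and nothing is added for paired wrists.
- **Abstract, Methods.** The same number is attached to people: "Forty subjects aged 20 to 80 years old and diagnosed as having mild to moderate CTS will be randomly assigned".
- **Section 2.6, Statistical analysis.** The paired t test is used within groups. Between groups, the independent t "test and chi-square will be used to evaluate and compare before and after treatments between two groups". No term for patient appears and no unit of analysis is named.

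The text mentions no study wrist, averaging of wrists, mixed model, GEE or clustered standard error.

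**The concern.** Putting both wrists of a bilateral patient in one arm makes the patient a randomised cluster of size one or two. The t tests and chi-square test treat every observation (or before-after pair) as independent. If two wrists from one person enter as two observations, the test credits the trial with more information than it has. The standard error is then too small, and P < .05 no longer carries a 5% false-positive rate.

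The primary outcome could be the worst case. Section 2.5.1.1 describes the BCTQ as self-reported and does not say whether it is completed per hand. If one score were attached to both wrists, the same number would count twice (correlation 1). Cross-sectional area and nerve conduction are measured on a wrist, so their correlation would be below 1.

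The sample size is also at stake. A figure that counts each wrist as independent overstates the power of any valid analysis once bilateral patients are enrolled.

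**Working it through.** **1. The plan's own figure.** The 40 wrists cannot be reproduced forwards, because no effect size or standard deviation is stated. Working backwards: 40 × (1 − 0.20) = 32 evaluable wrists, 16 per arm. For a two-sided 0.05 test with 80% power, the standardised difference is √(2 × (1.960 + 0.842)² / 16) = 0.99 (1.02 with the t distribution). So 40 fits a calculation in which every wrist is independent.

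**2. Assumed inputs.** The documents do not give b, the proportion of patients with both wrists enrolled, or ICC, the correlation between a patient's two wrists. I take b = 25%, 50% and 100%, and ICC from 0.2 to 1.0.

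**3. Formulas.**
- Share of wrists in bilateral pairs = 2b/(1 + b): 0.40, 0.667 and 1.
- Design effect DE = 1 + ICC × share.
- Naive SE / true SE ≈ 1/√DE.
- True type I error ≈ 2 × [1 − Φ(1.96/√DE)].
- Power of a valid analysis, if 80% holds under independence ≈ Φ(2.80/√DE − 1.96).

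**4. Results.** The simulated column is the ordinary independent t test under no effect, 16 wrists per arm, 100,000 runs. Whole patients only approximate the shares: 3, 5 or 8 bilateral pairs per arm.

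| Bilateral | ICC | DE | Naive/true SE | Type I, formula | Type I, simulated | Valid power |
|---|---|---|---|---|---|---|
| 25% | 0.2 | 1.08 | 0.96 | 5.9% | 5.9% | 77% |
| 25% | 0.5 | 1.20 | 0.91 | 7.4% | 7.2% | 73% |
| 25% | 1.0 | 1.40 | 0.85 | 9.8% | 9.6% | 66% |
| 50% | 0.2 | 1.13 | 0.94 | 6.6% | 6.4% | 75% |
| 50% | 0.5 | 1.33 | 0.87 | 9.0% | 9.0% | 68% |
| 50% | 1.0 | 1.67 | 0.77 | 12.9% | 13.4% | 58% |
| 100% | 0.2 | 1.20 | 0.91 | 7.4% | 7.4% | 73% |
| 100% | 0.5 | 1.50 | 0.82 | 11.0% | 11.4% | 63% |
| 100% | 1.0 | 2.00 | 0.71 | 16.6% | 18.5% | 51% |

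With no bilateral patients, or ICC = 0, DE = 1 and the test stays at 5%.

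**5. The other reading.** If each patient contributes one value, the tests hold 5%. If 40 is still a wrist count and every patient is bilateral, there are 40/2 = 20 patients. After 20% dropout 16 remain, 8 per arm, which is half the information assumed: DE = 2 and power about 51%. If 40 is a count of subjects, as in the abstract, both the 5% level and the sample size stand, but section 2.4.1 then names the wrong unit.

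**The case against.** Section 2.6 never says that wrists are the observations. It speaks of groups, section 2.2 randomises participants, and the abstract randomises forty subjects. On a per-patient reading the named tests are valid. This stands: wrist-level analysis is inferred from section 2.4.1 together with the bilateral rule. A reader might infer that the P values for the primary and every secondary outcome are certainly anti-conservative. The document does not support that, because it also requires that some bilateral patients are enrolled and that the within-patient correlation is positive.

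The inflation may also be small. If change scores are compared, the relevant correlation is that of the changes, which may be lower than that of the levels. At 25% bilateral and ICC 0.2 the error is only about 6%. A reader might likewise infer that a BCTQ score will be entered twice, or that the VAS is a wrist-level outcome. Sections 2.5.1.1 and 2.5.2.1 state neither.

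Finally, this is a condensed article, no analysis plan is at hand, and Figure 1 and Table 1 could not be read, so silence about a method for bilateral wrists is weak evidence. But the point does not rest on silence. The article states an allocation rule, a counting unit and a list of tests. Applied together to bilateral patients, they give invalid P values, and the only way out is a unit that contradicts section 2.4.1.

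**Conclusion.** The concern holds in conditional form. The unit is inconsistent (40 subjects against 40 wrists), and each reading that keeps the wrist count leaves something wrong once bilateral patients enter.

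- **Wrists analysed:** the nominal 5% test has a true error of about 6-10% with 25% of patients bilateral and about 6-13% with 50%, over ICC 0.2 to 1.0. The figure of about 18% is an extreme that needs every patient bilateral and one score counted twice.
- **One value per patient:** the error rate is right, but the wrist-based sample size can be short by up to half.

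The direction follows for any positive within-patient correlation. The size rests on the assumed 16 evaluable wrists per arm and on a bilateral share and ICC that the document does not supply.

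**What to change.** - In sections 2.2 and 2.6, state that the patient is the unit of randomisation and inference.
- Reconcile the forty subjects of the abstract with the 40 wrists of section 2.4.1.
- For the BCTQ, and any other score given once per patient, analyse one value per patient.
- For outcomes measured per wrist (cross-sectional area, nerve conduction, and VAS if rated per hand), prespecify one method: either the mean of the patient's affected wrists, which keeps the t tests already named, or a linear mixed model with a patient random intercept and small-sample degrees of freedom. Apply the same unit to the within-group paired tests.
- In section 2.4.1, restate the power with the design effect, giving the assumed bilateral share and ICC.

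**Cost.** The analysis change is wording and standard software, but it is not free. At 50% bilateral and ICC 0.5 to 1.0, confidence intervals widen by about 15% to 29% (√1.333 = 1.155; √1.667 = 1.291), and stated power falls from 80% to about 68% to 58%. Holding 80% would need 40 × 1.333 = 53.3 to 40 × 1.667 = 66.7, that is 54 to 67 wrists. The wider intervals are the correct ones.

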**Figure 1 F1:**
[figure not shown]
Study flow diagram.

**Figure 2 F2:**
[figure not shown]
Laser acupuncture with device at the PC7.

**Figure 3 F3:**
[figure not shown]
Acupoints used for carpal tunnel syndrome: 1. PC4, 2. PC6, 3. PC7, 4. PC8, 5. HT3, 6. HT7, 7. LU10, 8. LI4, 9. LI10, and 10. LI11.

### Interventions

2.3

#### Intervention group/real laser acupuncture group

2.3.1

Subjects in the intervention group will accept 3 sessions of real LA per week for 2 weeks (total 6 sessions). LA will be applied to each acupuncture point for 10 s with at least 4J/points based on the recommended LLLT treatment doses for CTS of the World Association of Laser Therapy (WALT).^[33]^

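### The stated laser settings (300 mW for 10 s) deliver 3 J per acupoint, not the minimum of 4 J that the protocol claims

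*Protocol article*

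**What the plan says.** The protocol article gives three figures that together fix the dose at each acupuncture point.

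- **Power.** Section 2.2 (Study design) describes the device "with a wavelength of 808 nm, power output of 300 mW and power density of 300 mW/mm^2". The Methods part of the abstract gives the same power and power density.
- **Time.** The abstract sets the exposure "with ten seconds of treatment for each acupuncture point". Section 2.3.1 repeats the 10 s.
- **Energy.** Section 2.3.1 states "LA will be applied to each acupuncture point for 10 s with at least 4J/points" and attributes the dose to a recommendation of the World Association of Laser Therapy (WALT).

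Ten acupoints are listed in section 2.2, and the schedule in section 2.3.1 is "3 sessions of real LA per week for 2 weeks (total 6 sessions". The article mentions no second power setting, no longer exposure and no repeat application at a point.

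**The concern.** For a laser of known output, the energy delivered follows from power and time; it is not a separate choice. Once 300 mW and 10 s are fixed, the joules per point are fixed too, and they do not reach the stated minimum.

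This matters because the dose is the experimental treatment. An operator who follows the power and time misses the protocol's own minimum at every point. An operator who works to the minimum must depart from the stated time or power. Nobody can adhere to all three, so treatment fidelity cannot be judged against the protocol.

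The objectives in the abstract, and the end of the Introduction, also make clear laser parameters one of the aims of the study. The inconsistency therefore sits in something the trial sets out to provide. A null result would be open to the objection that the dose fell short of the threshold the protocol set for itself. A positive result reported with the protocol's energy figure would pass a wrong dose to anyone trying to replicate it or compare doses across trials.

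**Working it through.** **Inputs**

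| Quantity | Value | Source |
|---|---|---|
| Power output | 300 mW = 0.300 W | Abstract (Methods); section 2.2 |
| Power density | 300 mW/mm² | Abstract (Methods); section 2.2 |
| Exposure per point | 10 s | Abstract (Methods); section 2.3.1 |
| Stated energy per point | at least 4 J | Section 2.3.1 |
| Acupoints | 10 | Abstract (Methods); section 2.2 |
| Sessions | 3 per week × 2 weeks = 6 | Abstract (Methods); section 2.3.1 |

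**Step 1: try to reproduce the stated energy.** Energy (J) = power (W) × time (s).

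0.300 × 10 = 3.0 J per point.

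The stated minimum of 4 J is not reproduced. The gap is 4 − 3 = 1 J, and 1/4 = 25% of the stated minimum.

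**Step 2: try the other readings.**

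- *From power density.* The spot area implied by the two figures is 300 mW ÷ 300 mW/mm² = 1 mm². Then 300 mW/mm² × 1 mm² × 10 s = 3.0 J, as before.
- *Pulsed output.* If 300 mW is peak power, pulsing lowers the energy; at an assumed 50% duty cycle it is 0.5 × 3.0 = 1.5 J. If 300 mW is the average power, the energy is still 3.0 J.
- *4 J as a cumulative or session total.* Over six sessions one point receives 6 × 3 = 18 J, and in one session ten points receive 10 × 3 = 30 J. Neither is a 4 J dose, and the wording gives the figure per point for a 10 s application.
- *A misprint or reading error in power or time.* Each appears in two places and agrees with itself. The energy figure appears once. If the energy figure is the misprint, it still has to be corrected.

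**Step 3: what would make the figures agree.**

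- Keep 300 mW and 4 J: time = 4 ÷ 0.300 = 13.3 s. In whole seconds, 13 s gives 3.9 J and 14 s gives 4.2 J, so 14 s is needed.
- Keep 10 s and 4 J: power = 4 ÷ 10 = 0.400 W = 400 mW.
- Keep 300 mW and 10 s: the energy is 3 J.

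**Step 4: the same gap over a course.** If each of the ten points is treated once per session on one side, a session delivers 30 J against at least 40 J. Six sessions deliver 180 J against at least 240 J. These totals are the 25% gap multiplied up; the protocol sets no target per session or per course.

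**The case against.** The strongest reply accepts the arithmetic and disputes its weight. An operator sets a power and a time, and both are stated consistently. The joule figure is derived from them, so the likeliest explanation is that a derived quantity was described wrongly while the treatment itself is clear. The sham arm has no output, so randomisation, blinding, type I error and outcome assessment are unaffected, and a null result would be a valid result for 300 mW over 10 s. Whether 3 J rather than 4 J is clinically too little depends on sources that are not at hand. A reader of the results could recompute the energy from the disclosed power and time.

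Much of this stands. The error does not bias the comparison between arms, and nothing here shows that 3 J is ineffective. The objection does not remove the contradiction, however. The text does not say which figure governs, and the 4 J is presented as a minimum with a stated basis, not as an incidental remark. A treatment that misses its own minimum when delivered as instructed is wrongly specified even if the comparison with sham is sound.

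It might also be said that a fuller protocol holds the detail. That document could show which figure was intended, but it could not make 300 mW, 10 s and at least 4 J all true.

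**Conclusion.** The concern holds. As written, the active treatment delivers 3.0 J per acupoint against a stated minimum of 4 J, a 25% shortfall at every point in every session.

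The conclusion assumes only that 300 mW is the output reaching the point throughout the 10 s; any loss or pulsing below that would widen the gap. It does not depend on what WALT recommends, because the conflict lies within the article. The document does not show which of the three figures is wrong.

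The damage is to the definition of the treatment, its fidelity and its reproducibility, not to the validity of the randomised comparison. It should be corrected all the same, because the dose is the intervention under test and clear laser parameters are among the stated aims.

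**What to change.** Check the actual device setting, decide which figure is intended, and make the abstract, section 2.2 and section 2.3.1 agree so that energy = power × time. The choice belongs to the sponsor and the device experts:

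1. **Lengthen the exposure** to 14 s per point at 300 mW (4.2 J). For ten points this takes 140 s instead of 100 s, or 40 s more per session on one side. Sham exposure must be lengthened equally so that the two procedures stay indistinguishable.
2. **Raise the power** to 400 mW for 10 s, if the device allows it. The stated power density must then be revised as well: 400 mW/mm² if the spot stays at 1 mm².
3. **Restate the dose** as 3 J per point, and withdraw or rewrite the claim that it meets the recommended minimum of 4 J.

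The article places the trial in 2019 and does not show whether enrolment has begun. If it has not, make the correction before the first patient is treated. If it has, do not change the regimen merely to match the text; establish what was delivered, correct the description, and report that energy with the results.

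The cost is a device check and a short protocol correction, with no extra patients or visits.
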